## Abstract

**Background:**

People with dementia (PWD) experience ten times as many incident falls as people without dementia. Little is known about how best to deliver services to people with dementia following a fall. We used an integrated, mixed-methods approach to develop a new intervention which combines theory generated via a realist synthesis and data on current provision and pathways, gathered through a prospective observational study as well as qualitative interviews, focus groups and ethnographic observation. This intervention is to be tested in a feasibility study in the UK National Health Service.

**Methods:**

People living with dementia in one of three geographical areas will be eligible for the study if they experience a fall requiring healthcare attention and have an informal carer. Potential participants will be identified by community services (primary care, paramedics, telecare), secondary care (ED, facilitated discharge services, rehabilitation outreach teams) and research case registers. Participants will receive a complex multidisciplinary intervention focused on their goals and interests for up to 12 weeks. The intervention will be delivered by occupational therapists, physiotherapists and rehabilitation support workers. Feasibility outcomes will include recruitment and retention, suitability and acceptability of outcome measures and acceptability, feasibility and fidelity of intervention components. PWD outcome measures will include number of falls, Montreal Cognitive Assessment (MOCA), European Quality of Life Instrument (EQ-5D-5L), Quality of Life–Alzheimer’s Disease Scale (QOL-AD), Modified Falls Efficacy Scale (MFES) and Goal Attainment Scaling (GAS). PWD outcome measures completed by an informal carer will include Disability Assessment for Dementia (DAD), EQ-5D-5L Proxy, QoL-AD Proxy and a Health Utilisation Questionnaire (HUQ). The carer outcome measure will be the Zarit Burden Interview (ZBI). An embedded process evaluation will explore barriers and facilitators to recruitment and intervention delivery.

**Discussion:**

The study results will inform whether and how a larger multicentre RCT should be undertaken. A full RCT would have the potential to show how outcomes can be improved for people with dementia who have fallen.

**Ethics and dissemination:**

The National Research Ethics Service Committee Newcastle and North Tyneside 2 approved the feasibility study.

**Trial registration:**

International Standard Randomised Controlled Trial Registry. Registration number: ISRCTN41760734. Date of registration: 16/11/2015.

**Electronic supplementary material:**

The online version of this article (10.1186/s40814-018-0364-7) contains supplementary material, which is available to authorized users.

## Background

Recent estimates suggest that there are 850,000 people living with dementia (PWD) in the UK, which will increase to over 1 million by 2025 and 2 million by 2051 if current trends remain stable [1]. While the number of people with dementia in care settings has increased, most individuals with dementia still live in the community [2]. The annual prevalence of falls in PWD ranges from 47 to 90%, depending on dementia subtype, with PWD living in their own home sustaining almost ten times more falls per year than cognitively intact older people. [3]. Their falls are more likely to be injurious than those of controls. Where injuries are sustained, PWD are less likely to recover well than other older people [4]. Falls and fall-related injuries are therefore a significant cause of morbidity and mortality in PWD.

There is presently limited evidence to guide the management of falls and fall-related injuries in people with dementia, and available evidence tends to be focused on those who sustain more serious injuries, such as fractures [5–10]. While multifactorial falls services can prevent further falls in cognitively intact older people [11, 12], their effectiveness for people with dementia has not been demonstrated [13]. Yet, there are potentially substantial benefits to be gained if the outcome of these falls and injuries in PWD could be improved. For example, a successful intervention has the potential to reduce psychological morbidity and improve wellbeing [14]. There is also evidence to suggest that rehabilitation interventions can improve physical functioning in people with cognitive impairment following hospital admission [15, 16] and that exercise may reduce the risk of future falls in this patient group [17].

The overall aim of this study is to assess whether it is possible to design a complex intervention to reduce falls in PWD living in their own homes who have sustained a fall requiring healthcare attention. The intervention was developed in earlier phases of the study (using an integrated, mixed-methods approach to develop a new intervention which combines theory generated via a realist synthesis and data on current provision and pathways, gathered through a prospective observational study as well as qualitative interviews, focus groups and ethnographic observation). We are now conducting a study to assess the feasibility and acceptability of the intervention and selected study procedures, and identify any changes needed prior to a full-scale randomised controlled trial (RCT).

## Objectives

### Primary objective

The primary aim of this study is to determine whether to progress to a full-scale randomised controlled trial which aims to reduce falls in PWD who have sustained a fall requiring healthcare attention.

### Secondary objectives

The secondary aims of this study are to determine the recruitment and retention rates from a range of settings, to identify issues related to the suitability and acceptability of outcome measures, and to assess the factors influencing the acceptability and implementation of the intervention.

## Methods

This is a single arm feasibility study of the study intervention. We have followed the Standard Protocol Items: Recommendation for Interventional Trials (SPIRIT) guidance [18] and the SPIRIT checklist is provided in Additional file 1. In developing the intervention and designing the feasibility study, we have followed the Medical Research Council (MRC) guidance on developing and evaluating complex interventions [19]. We provide a description of the intervention using the Template for Intervention Description and Replication (TiDieR) guidelines [20] in Additional file 2. In accordance with the MRC guidance on process evaluation of complex interventions [21], we have developed a logic model (to be reported elsewhere). The study will be carried out in three research sites, reflecting a range of National Health Service (NHS) practice to allow for generalisability.

### Recruitment, screening and consent

We plan to recruit a minimum of 30 people with dementia (PWD) and 30 informal carers for the intervention and up to 28 professionals for the process evaluation (beginning 5th February, ending 29th April 2018). Participants will be recruited from three geographical areas in the UK (Newcastle upon Tyne, Norwich and Stockton upon Tees).

### Inclusion criteria for people with dementia

A known diagnosis of dementia (any subtype), made prior to entry into the study, by a specialist in dementia care (Geriatrician, Neurologist or Old Age Psychiatrist).Must have sustained at least one fall requiring healthcare attention (via 111 (a free-to-call single non-emergency number medical helpline operating in England and Scotland), district/practice nurse or minor injuries unit as well as the services outlined below), within 1 month prior to their identification as a potential study participant. A fall will be defined as an event whereby a person comes to lie on the ground or another lower level with or without loss of consciousness. The fall leading to their identification will be known as the index fall.Must be dwelling in the community at the time of the index fall and returning to the community at the time of the intervention.Must have an informal carer available to assist with completion of the diaries.Either has capacity to consent to participation, or a personal or nominated consultee who is able to give an opinion on the participation of the PWD.

### Exclusion criteria for people with dementia

Diagnosis of dementia cannot be confirmed by the primary care team within 2 weeks of their being identified as a potential participant.Participant found to be dwelling in residential or nursing care, or to have been a hospital inpatient at the time of the index fall.Participant refuses consent, or lacks capacity and does not have personal or nominated consultee, or their personal or nominated consultee declines participation.Not able to communicate in English either because they are not a native English speaker or due to advanced dementia.Informal carer declines participation in the study.

### Identification and recruitment of people with dementia

We will compare the ease of identification of PWD via three main routes (community settings; secondary care settings; research registers); this will inform potential recruitment strategies for a future definitive trial of the developing an intervention for fall related injuries in dementia (DIFRID) intervention.

Community services used for recruitment are primary care, paramedic services and telecare services. Secondary care services used to identify potential study participants are emergency departments (ED), supported discharge teams and rehabilitation outreach teams. We will also recruit potential participants from the North East (NE) and North Cumbria (NC) Clinical Research Network (CRN) Case Register and Join Dementia Research (JDR).

At each stage of the recruitment procedure, a list of all potential participants who had contact with the research study will be maintained at each site. If the person has declined or not responded to an invitation from the research team or not been recruited for another reason then they will not receive any further contacts from the research team.

### Confirmation of PWD eligibility

With the exception of potential participants identified through primary care (who will have been identified via the Quality and Outcomes Framework (QOF) dementia register), we will have to confirm that the participant has a diagnosis of dementia prior to formal recruitment to the study. At first identification in the relevant setting, participants will be given or posted a summary participant information sheet (PIS). In community settings, participants will be asked to send in an opt in form giving their contact details. In secondary care settings, it will be possible to access contact details via patient notes. After they have received the summary, all potential participants will be contacted by the clinical trials associate (CTA) by telephone. During the initial telephone call from the CTA to discuss participation, the CTA will seek verbal consent to contact the general practitioner (GP) practice to check whether the person is on the dementia QOF register. If secondary care records indicate that the person should be on the QOF register the GP will be invited to update the QOF register to include this person.

If the participant is on the dementia QOF register, the CTA will send a full PIS. A clinical researcher will contact them again to confirm eligibility and, if still interested, to arrange a home visit to take consent and undertake a baseline assessment if appropriate. Participants who are not on the dementia QOF register will be sent a letter explaining that they are not eligible but thanking them for their interest in the study.

### Consent

Participants will be required to give informed consent to participation in the intervention study in accordance with the Declaration of Helsinki. Due to the nature of dementia, some participants may lack the capacity to give full informed consent. In this case, the provisions of the Mental Capacity Act (2005) will apply. PWD will be asked to give consent appropriate to their level of understanding, ranging from written informed consent to account being taken of verbal and non-verbal communication in determining willingness to participate. In those individuals found to be without capacity to give full informed consent, the CTA will identify a personal or nominated consultee and seek their advice regarding participation by letter and/or phone call. If a consultee thinks that the person would not have wanted to participate in the study, the participant will not be recruited and they will not be contacted any further about the study. If they do not give an opinion, it will be assumed that consent is withheld and they will not be recruited or contacted further about the study. Any PWD appearing distressed by participation or withdrawing consent will be excluded from the study without prejudice to clinical care.

### Identification and recruitment of informal carers

We anticipate that many PWD seeking healthcare attention will be accompanied by an informal carer. In this situation, the informal carer will be aware of the study from the outset. They will be issued with an informal carer PIS by the CTA at the earliest opportunity. If PWD are not accompanied by an informal carer, we will ask them to identify if they have an informal carer who might be interested in being involved in the study with them.

### Recruitment to the process evaluation

The initial consent process with PWD and informal carers will include consent for optional participation in the qualitative aspects of the study. We will purposively select a sample of consenting PWD and informal carers for observation and interview. Examples of participant characteristics which will be considered when sampling will include gender, falls history, goals and activities identified for the intervention, intensity of the intervention and adherence to the intervention (through participant diaries and discussions with the therapists delivering the intervention). We will aim to observe the delivery of all components of the intervention in all sites assuming this is logistically possible. This will enable us to explore whether and how the sessions are tailored to individuals, activities are embedded into usual routines and the role of the informal carer in the intervention.

Consent will be sought from all professionals with the exception of those involved in developing, training and supervising the intervention and those directly involved in delivering the intervention. Participation in observation and/or interviews and informal discussions will be part of their role and therefore not optional. A PIS will be provided to make these expectations clear and to outline the rationale for these qualitative aspects of the study.

To ascertain the ‘fit’ of the intervention with existing services, and the impact on referral patterns, we will liaise with the multidisciplinary team (MDT) and staff delivering the intervention to identify where referrals have been made. As part of their initial assessment, the physiotherapist and occupational therapist will explore current support services being used by the PWD. We will use information from the assessment to identify a purposive sample of staff whom we would like to interview. Selected professionals will be sent an invitation letter and PIS. This will be followed up by a telephone call within a week to check whether the professional is willing to take part and, if so, to arrange a meeting to take consent and conduct the interview.

CTAs responsible for recruitment and professionals involved in making the initial approach will be sent a PIS by the qualitative team towards the end of the recruitment period. This will be followed up by email or telephone to discuss participation and, if appropriate, arrange the interview.

### Data collection and follow up

#### Baseline assessments and data

Baseline data for the outcome measures described below will be recorded by a clinical researcher for PWD and informal carers consenting to the intervention study within 2 weeks of confirmation of eligibility (Table 1).

**Table 1 Tab1:** Assessment of outcome measures

	Completed by	Time to complete	Baseline visit	12-week follow-up visit
MOCA	Patient	10 min	✓	
EQ-5D-5L	Patient	5 min	✓	✓
QOL-AD	Patient	5–10 min	✓	✓
MFES	Patient	5–15 min	✓	✓
GAS	Patient	20–40 min	✓^a^	✓^a^
TUAG	Patient	5 min	✓^a^	✓^a^
DAD	Informal carer (proxy)	15 min	✓	✓
EQ-5D-5L	Informal carer (proxy)	5 min	✓	✓
QOL-AD	Informal carer (proxy)	5–10 min	✓	✓
HUQ	Informal carer (proxy)	20 min		✓
ZBI	Informal carer	10 min	✓	✓

^a^This measure will be completed with the therapist after the initial assessment and repeated at the final intervention visit

After the baseline assessment, the clinical researcher will send a referral to the intervention team using a structured referral form with details of the baseline assessments of the PWD and informal carer. The intervention team will then arrange an initial intervention assessment within 2 weeks.

#### Follow up assessments

At 12 weeks, the clinical researcher will carry out a second visit to repeat most of the outcome measures completed at the baseline assessment with PWD and informal carers (see Table 1). The exception is the Montreal Cognitive Assessment (MOCA); completing this at baseline will enable us to describe the cognitive function of participating PWD, but it will not be repeated as the intervention is not expected to have an impact on cognition. The Health Utilisation Questionnaire (HUQ) will be completed by the clinical researcher with the informal carer on behalf of the PWD to determine the use and health and social care services by the PWD in the preceding 12 weeks.

### Outcome measures

#### PWD outcome measures

All outcome measures will be completed by those PWD with the capacity to do so. With the exception of the MOCA, all measures will be completed at baseline and 12 week follow-up (see Table 1). The schedule of events is shown in Table 2.

**Table 2 Tab2:** Schedule of events

	Baseline assessment (clinical researcher)	Week 1 (intervention)	Weeks 2–12 (intervention)	Week 12 follow-up assessment (clinical researcher)
Informed consent (including consent for observation and/or interview)	X			
Baseline data collected (see Table 1)	x			
2 Assessment visits by intervention team including timed up and go test		X		
Up to 22 visits by Intervention team. Final visits will include goal attainment scaling and timed up and go test			X	
Completion of diary			X	
Informed consent of professionals and participants and observation of interventions received		X	X	
Informed consent and qualitative interview with some professionals regarding views on intervention.			X	
Qualitative interview with patients, informal carers and professionals views on intervention			X	
Follow up outcome data collected (see Table 1)				X

#### Number of falls

This will be assessed through prospective completion of a diary throughout the 12-week intervention with the aid of an informal carer when required. Participants will be asked to record whether they had any falls on each day and, if so, to describe the context and consequences of the fall. These data will be used to calculate the proportion of participants with one or more falls and the fall rate per person year.

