### Adverse events

This is a non-drug intervention trial, using interventions that might be offered as part of a routine physiotherapy intervention. Dementia is progressive and associated with comorbidity. Inter-current illness will be very common. We will aim to achieve a balance between ensuring that any adverse events (AEs) which are likely to be related to the study are detected, and the recording of numerous unrelated events.

Falls, injuries, deaths and hospital admissions will be ascertained prospectively throughout the study. They will be recorded through diaries which will be reviewed regularly by the therapists and/or rehabilitation support workers.

We will define an AE as an incident, injury or symptom related to therapy sessions, or activities undertaken independently. The most likely AEs are fatigue, minor musculoskeletal symptoms or injuries such as muscle stiffness, or sprains, or increased falls though increased activity. Some conditions such as arthritis or angina may be exacerbated by exercise. AEs will be monitored by therapists and rehabilitation support workers, and reported where they occur. All serious AEs should be reported to the NHS Research Ethics Committee (REC).

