#### Quantitative analyses

The main analysis will be of feasibility outcomes. We will report the numbers of eligible participants seen over the recruitment period, and the resulting rates of recruitment, retention and data completion. Non completers will be characterised. We will also assess performance of potential outcome measures for a definitive trial. We will ascertain data completeness of the instruments and any potential bias in the completion of follow-up data to inform the choice of instruments in a future trial. The majority of the outcome data will be presented in simple descriptive tables presenting percentages, means and standard deviations.

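### The falls diary item, as described, secures whether a participant fell on a day but not how many times, so the planned fall rate per person-year can be understated (minor)

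*Protocol article*

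**What the plan says.** The protocol article, Outcome measures, has an entry headed Number of falls. It gives three facts.

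- **Source.** "This will be assessed through prospective completion of a diary throughout the 12-week intervention with the aid of an informal carer when required".
- **Item.** "Participants will be asked to record whether they had any falls on each day and, if so, to describe the context and consequences of the", with the event named in the singular. The question is whether any falls happened that day, and the follow-up refers to a single fall. No number per day is requested. No rule is stated for a day with more than one fall.
- **Use.** "These data will be used to calculate the proportion of participants with one or more falls and the fall rate per person year".

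The Adverse events section uses the same diaries to pick up falls, injuries, deaths and admissions, and adds: "They will be recorded through diaries which will be reviewed regularly by the therapists and/or rehabilitation support workers".

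On the standing of the outcome, Quantitative analyses says: "The main analysis will be of feasibility outcomes". The same section also plans to assess how candidate outcome measures for a definitive trial perform. The Primary objective describes that trial as one meant to reduce falls. The diary form itself is not shown.

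**The concern.** The item and one of its two planned summaries do not match. The share of participants who fall at all needs one bit of information per person, which a daily yes/no supplies. A rate per person-year needs the number of events, and the described item does not ask for it. If the form follows the text, an analyst cannot later recover a count that was never requested.

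The loss can go only one way: a day with two or more falls may be recorded as one, and a day with one fall cannot become two. It falls on participants who fall repeatedly. That is a realistic group here, since the Background describes "PWD living in their own home sustaining almost ten times more falls per year than cognitively intact older people".

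What is at stake is the quality of a candidate outcome measure, in a study that sets out partly to see whether such measures work. A diary that leaves the count to chance would carry that weakness into the later trial's main outcome.

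**Working it through.** **No stated figure to reproduce.** The article gives no fall rate, no power calculation and no frequency of several falls on one day. Everything below rests on assumed inputs and shows how large the loss would be in the worst case, where only one fall is counted per positive day.

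**Inputs**

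- From the article: a 12-week diary (84 days), and "We plan to recruit a minimum of 30 people with dementia (PWD) and 30 informal carers for the intervention".
- Assumed: a true rate L of 4 to 15 falls per person-year. Between-person variation is either none or gamma with shape k = 0.5.

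Let x = L/365.25 be the mean number of falls per day.

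**1. Falls independent, one common rate (Poisson).** Share of days with a fall = 1 − exp(−x). Understatement = 1 − [1 − exp(−x)]/x.

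- L = 4: x = 0.010951, 1 − exp(−x) = 0.010892, understatement 0.5%.
- L = 15: x = 0.041068, 1 − exp(−x) = 0.040236, understatement 2.0%.

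**2. Rates vary between people (gamma, k = 0.5).** Share of days with a fall = 1 − (1 + x/k)^(−k).

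- L = 4: 1 − 0.989225 = 0.010775, understatement 1.6%.
- L = 15: 1 − 0.961301 = 0.038699, understatement 5.8%.

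Without same-day clustering the range is therefore about 0.5% to 6%.

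**3. Same-day clustering.** If a share q of fall-days holds m falls on average, and the other fall-days hold one, understatement = 1 − 1/[1 + q(m − 1)].

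| q | m | Understatement |
|---|---|---|
| 5% | 2 | 1 − 1/1.05 = 4.8% |
| 10% | 2 | 1 − 1/1.10 = 9.1% |
| 20% | 3 | 1 − 1/1.40 = 28.6% |

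These values are almost a restatement of the assumed q and m. They show sensitivity and are not an estimate for this study.

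**4. Set against precision.** Exposure is 30 × 84/365.25 = 6.9 person-years if everyone completes the diary. At 4 to 15 falls per person-year that is about 28 to 103 falls. The Poisson relative standard error is 1/√28 = 19% down to 1/√103 = 10%. With gamma shape 0.5 it is √[(1/μ + 1/k)/30], where μ = 84L/365.25 is 0.92 to 3.45 falls per person, giving 32% down to 28%. Without clustering, the bias is well below the random error.

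**5. What does not change.** A participant with any positive day is a faller under either recording rule, so the share of participants who fall is identical. The progression criteria concern consent, session attendance, retention, fidelity and acceptability, and none uses a fall count.

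**The case against.** The best case against the point has four parts.

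- **The item is more than a yes/no.** It also asks for an account, and the question is put in the plural, so two falls on one day could be read from the narrative. This is true. But the prompt is about one fall, the writer is a person with dementia helped by a carer when needed, and the narrative is not described as the source of the count.
- **Staff review the diaries.** With up to 24 visits in 12 weeks, therapists could clarify entries. This would catch some repeats. It is, however, described for adverse-event detection and not as a step in counting falls.
- **A journal article condenses.** The diary form or full protocol may already ask for a number. That is possible and limits what can be concluded. Still, the article is not silent here: it prints the recording rule and the statistic drawn from it, and the two do not fit.
- **Little depends on it here.** Falls are described, not tested, in a single arm of about 30 people. This stands and sets the severity.

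A reader might infer more than the text supports. Nothing says that several falls on one day are scored as one, so it cannot be said that the planned rate *is* a rate of fall-days. Nor does the article say that this study supplies the later trial's baseline rate: its falls are recorded during the intervention. It plans no overdispersion estimate. And with no comparison group or pre-intervention diary, there is no treatment contrast that the item could hide.

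**Conclusion.** The point holds as a minor one. The described item secures the share of participants who fall, but it does not secure the number of falls needed for the rate. Repeat falls on a day enter the count only by way of free text or staff review, so the rate can be too low and cannot be too high for this reason.

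The size is about 0.5% to 6% without same-day clustering. This assumes 4 to 15 falls per person-year, between-person variation from none to gamma shape 0.5, and no rescue of repeats from narrative or review, so it is an upper bound for those settings. With clustering the loss is larger, but the documents give nothing from which to say how much. The feasibility conclusions and the stop/go decision do not depend on it. The reason to act is that the diary is a candidate instrument for a trial whose aim is to reduce falls.

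**What to change.** Have the diary ask for the number of falls each day (0, 1, 2, and so on), with one context-and-consequences entry for each fall. Compute the rate per person-year from the summed number of falls. Derive the share of participants who fall from the same field, as any day with a count above zero.

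If the diary form already records a number per day or logs each fall separately, only the article's sentence needs correcting to say so.

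The cost is one reworded diary item or one reworded sentence. No visits are added. The downside is slightly more writing for participants and carers on days with several falls.
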